### Analysis of blood samples

Sample aliquots and DBS will be shipped to the central laboratories in Bangkok, Thailand where they will be analysed. All laboratory activities will be performed by experienced and trained staff. All laboratory procedures will be performed using validated SOPs. Multiplex serology tests based on Luminex xMAP Intelliflex System will be developed and validated for measures of IgG and IgM of common pathogens causing fever; all other methods have already been published in peer-reviewed journals.

Malaria quantitative PCR (qPCR) will be performed for all participants to identify individuals with malaria parasites. The PCR methods typically have a detection level in the range of 100–1000 parasites per millilitre.^35^ Genus-specific qPCR targeting Plasmodium *18S rRNA* genes will first be performed to screen for positive individuals, and then species-specific assays will be performed to differentiate the parasite species (*Plasmodium falciparum*, *Plasmodium vivax*, *Plasmodium malariae*, *Plasmodium ovale* and *Plasmodium knowlesi*).^36–39^

Serology tests for selected common pathogens causing fever including IgG and IgM for Dengue, Chikungunya, Japanese encephalitis, Zika, SARS-CoV-2, *P. vivax*, *P. falciparum*, *Orientia tsutsugamushi*, *Rickettsia* spp and *Leptospira* spp will be performed for all participants.

Tests for hepatitis B and C: all participants will be tested for HBV surface antigen; participants 15 years or older will also be tested for IgG for HCV, and the positive samples will undergo HCV PCR.

Non-communicable disease-related markers: participants 15 years or older will be tested for Haemoglobin A1c, total cholesterol and high-density lipoprotein cholesterol.

Additionally, the remaining samples will be tested for exposure to, or presence of, pathogens associated with selected diseases that are regionally or locally prevalent or important. The final list of diseases, pathogens and sample selection will be adjusted based on findings from other SEACTN studies exploring diagnostics and prognostics in febrile patients, and other available evidence.

### Results feedback

Individual-level data collected from physical examinations and haemoglobin tests will be provided on the same day once all field procedures are concluded for an individual participant (section: Study procedure—Information, consultation and referral). Additionally, participants will be thoroughly informed about the implications of the laboratory tests to be performed during the consent process. They will be presented with the option to receive the results of hepatitis B and C tests. If they wish to receive them, the results, once available, will be placed in a sealed envelope and will then be delivered by the local health providers or village leaders to the participants. It is anticipated that there will be a delay of approximately 6 months to 1 year from sample collection to results feedback. The time frame encompasses the completion of data collection at the entire site, transportation of samples to Bangkok, sample management, analysis and the subsequent return of results. The decision on which results to provide to individual participants is made in consultation with the site research teams and local clinicians, considering factors such as their clinical relevance, the potential harm that could result from a lack of consultation on results distribution and the accessibility of treatment.

### Planned analysis

All data obtained through questionnaire interviews, physical examinations and haemoglobin point-of-care tests will be collected on tablets using an electronic data collection platform—Open Data Kit.^40^ The electronic case report form has built-in validation rules to identify missing or potentially incorrect data. Stringent checks are applied to variables used to estimate the study outcomes, such as recent fever history, diabetes history and weight. Survey interviewers cannot progress to the next question if these data are missing or outside the defined ranges. Throughout the survey, data will be continuously updated and monitored for quality. Data queries and quality reports will be generated every two to 4 weeks for data verification and correction, and to identify areas needing additional training and support, ensuring data integrity.

For descriptive summaries, means and SDs or medians with IQR for continuous variables, and proportions for categorical variables will be calculated. Outcomes will be presented as an overall estimate by country, and with 95% CIs, stratified and compared across sites and participants’ sociodemographic characteristics using appropriate tests, such as the Student’s t-test, Mann-Whitney U tests or χ^2^ tests. Associations between disease status, risk factors, self-perceived health status and other characteristics will be explored through univariate and multivariate analyses, and measures of effect will be reported with 95% CIs. Sampling weights will be accounted for, as needed, in the analysis.

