### Sample size

This study is adequately powered to determine the prevalences of all key indicators within each age group, with a design effect of 1.5 and a range of 5%–10% degrees of precision, while considering a maximum of 1500 participants per study country (table 1). To account for a 10% non-response rate, assuming an average household size of 4.5 persons, and enrolling all household members, the final sample size was adjusted to 1667 participants per country.^19–21^

**Table 1 T1:** Required sample size tested against the estimated prevalence of key indicators of the highest prevalence, overall and by age groups of interests

	Expected number of participants	Indicator (estimated prevalence)	Required sample size*
Overall	1500	Overweight (20%)	369
Age groups (years)			
≥15	1050	Current drinker (55%)	570
<5	150	Anaemia (30%)	122
15–49	750	Injury or death caused by recent accident (20%)	414
≥50	300	Hypertension (20%)	257

n: sample size; DEFF: design effect. Design effect of 1.5 is used to account for a slightly expected increase in variance due to clustering; N: population size; p: expected prevalence of key indicators; d: degree of precision.

*The formula used for calculating sample size is shown above. Assessing the sufficiency of the sample size for the key indicators of the highest prevalences ensures sufficient statistical power for indicators with lower prevalence. A degree of precision of 5% is applied for the sample size calculation overall and across age groups, except for the under 5 years and the 50 years or older groups, for which degrees of precision of 10% and 6% are applied, respectively.

The minimal sample size required was calculated based on the estimated prevalences of key indicators overall and within each population age group (table 1). Prevalence estimates, population proportions within each age group and average household size were derived from previously conducted national health surveys and published studies, preferably from the study country, or from countries with a similar epidemiological context.^19–29^ When the estimated prevalence of an indicator varied across study country, the highest prevalence estimates were applied.

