The household section is completed by the household head, providing information on household characteristics and a list of all household members along with any illnesses in the past 4 weeks and health seeking behaviour.The adult section is for household members aged 15 years or older and includes questions on sociodemographic characteristics (eg, age, sex, education, marital status and occupation), disease history (eg, tuberculosis, diabetes, cardiovascular disease), self-perceived health status, health concerns, substance use (eg, tobacco and alcohol) and other disease risk factors.The women’s health section is for female household members aged 15 years or older and includes questions on contraception use, utilisation of antenatal care and delivery services.The children’s health section is answered by caretakers of children under 5 years, providing information on each child’s vaccination and breastfeeding history.

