The study will also bridge the gap in community-based seroprevalence estimates for common pathogens causing fever, minimising biases related to health-seeking behaviour in facility-based studies. The data can also to be used for population-based incidence estimates.^41 42^ Furthermore, the updated prevalences of hepatitis B and C can be instrumental in evaluating the coverage and effectiveness of HBV vaccination programmes, and inform HCV screening and treatment strategies in the region in the era of direct-acting antiviral agents.^43 44^ This study also extends its scope to gather insights into the health perspectives and concerns of community members, facilitating the alignment of future interventions with the needs and expectations of the population. Specifically, for self-perceived status, while existing studies primarily focus on the elderly population, this study encompasses a broader age range.^45–48^ This can inform tailored interventions to improve the quality of life for a more extensive population.^49–51^

This study encourages regional collaboration by applying consistent research methods and seeking representative samples across study sites, allowing effective cross-country comparisons and fostering collaborative approaches to address shared health challenges.^3^

The findings of this study are limited in their generalisability and should be interpreted with caution when considering broader implications for rural populations in the study countries. However, the study was specifically designed for and conducted within the selected rural areas of Bangladesh, Cambodia and Thailand, where SEACTN is operational. This focused approach allows for insights into health challenges and opportunities within these areas. The cross-sectional design and observational nature of the study is at risk of, such as temporal bias, selection bias and participation bias. However, to minimise the bias as much as possible, we designed the survey with appropriate evaluation methods, and adequate training and supporting material will be well prepared for the field work.

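### The tests named for comparing sites are unadjusted, so between-country differences in age-dependent outcomes may partly reflect age and sex structure

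*Protocol article*

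**What the plan says.** The "Planned analysis" section sets out the comparison in one sentence. It opens with "Outcomes will be presented as an overall estimate by country, and with 95% CIs, stratified and compared across sites" and goes on to the methods: "stratified and compared across sites and participants’ sociodemographic characteristics using appropriate tests, such as the Student’s t-test, Mann-Whitney U tests", with chi-square tests as the third example. The legend of Figure 1 shows one site in each of Bangladesh, Cambodia and Thailand, so comparing sites means comparing countries.

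Two other statements in the section bear on adjustment. Associations among disease status, risk factors, self-perceived health and "other characteristics will be explored through univariate and multivariate analyses, and measures of effect will be reported with 95% CIs". On weighting, "Sampling weights will be accounted for, as needed, in the analysis".

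"Questionnaire interviews" lists "sociodemographic characteristics (eg, age, sex, education, marital status and occupation" among the items collected from adults, so age and sex are among the planned stratifiers. The Discussion says that consistent methods and representative samples have the effect of "allowing effective cross-country comparisons and fostering collaborative approaches to address shared health challenges". Age or sex standardisation is not mentioned anywhere in the article.

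**The concern.** Many of the primary outcomes plausibly rise with age: hypertension, diabetes, raised cholesterol, overweight and cumulative IgG exposure. An overall prevalence is the average of the age-specific prevalences, weighted by the site's age distribution. Two sites with the same prevalence at every age will differ overall if one population is older. A t, Mann-Whitney or chi-square test on the overall figures cannot separate that from a difference at given ages, and an age difference can equally hide a real one.

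Representative sampling does not help here. It reproduces each site's own age structure faithfully, and sampling weights do the same. That is right for describing one site, but it is not enough for explaining a difference between two. The Discussion rests the value of the cross-country comparison on just these features, and its list of biases (temporal, selection, participation) does not include differing population structure. A reader could then take a difference in composition for a difference in risk.

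**Working it through.** **Inputs from the article ("Sample size" and Table 1).** Adults aged 15 or over: 1050 per country. Aged 50 or over: 300. Design effect: 1.5. Hypertension at 50 or over: 20%. One age split serves all countries: "Prevalence estimates, population proportions within each age group and average household size were derived from previously conducted national health surveys". No split by site is given.

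**Check of the plan's own figure.** Table 1's required sample for hypertension follows from n = DEFF × z² × p(1−p)/d² = 1.5 × 1.96² × 0.20 × 0.80 / 0.06² = 256.1, stated as 257. The design effect and prevalence are thus used here as the plan uses them. The plan sizes precision within a country; it gives no target difference or power for a between-country test.

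**Assumptions not in the article.** Two sites have identical age-specific prevalence. Prevalence at 15–49 is 10%. Prevalence at 50 or over is 20% (Table 1's hypertension figure) or, as a steeper gradient, 40%. The share of adults aged 50 or over differs by 5 to 20 points around 300/1050 = 28.6%.

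**Formulas.** Crude prevalence at a site with share s aged 50 or over is p = 0.10 + (p50 − 0.10) × s. The crude difference is therefore (p50 − 0.10) × the gap in s. Effective sample size is 1050/1.5 = 700 per site. The standard error is √{[p1(1−p1) + p2(1−p2)]/700}. The rejection probability is for a two-sided 5% test, counting rejections that favour the older site (2.5% if there were no difference).

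| Prevalence at 50+ | Gap in share 50+ | Crude prevalences | Difference | Rejection |
|---|---|---|---|---|
| 20% | 5 points | 12.6% v 13.1% | 0.5 points | 5% |
| 20% | 10 points | 12.4% v 13.4% | 1.0 points | 8% |
| 20% | 20 points | 11.9% v 13.9% | 2.0 points | 20% |
| 40% | 5 points | 17.8% v 19.3% | 1.5 points | 11% |
| 40% | 10 points | 17.1% v 20.1% | 3.0 points | 30% |
| 40% | 20 points | 15.6% v 21.6% | 6.0 points | 82% |

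**Worked rows.** At 20% with a 20-point gap, the shares are 18.6% and 38.6%, SE = √{(0.1045 + 0.1194)/700} = 0.0179, z = 0.020/0.0179 = 1.12, and rejection is about Φ(1.12 − 1.96) = 0.20. At 40% with the same gap, SE = √{(0.1315 + 0.1692)/700} = 0.0207, z = 0.060/0.0207 = 2.90, and rejection is about 0.82. Counting both tails alters only the smallest effect noticeably (4.6% becomes 5.9%).

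**After standardisation.** With any common standard share S, both sites have prevalence 0.10 + (p50 − 0.10) × S, so the expected difference is 0 in every row.

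**The case against.** The strongest reply is that this is a condensed article. Standardisation and model covariates are normally left to a full protocol or analysis plan, and the tests are introduced only as examples. The same sentence plans stratification by sociodemographic characteristics, age and sex among them, and the multivariate analyses could include site. The primary objectives are prevalences, none of them a between-country contrast, and crude prevalence is the correct target for local burden and resource allocation. A crude difference of this kind is also real; it misleads only if read as a difference at given ages.

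Much of this stands. The text leaves adjustment open, and crude prevalence by site should stay. What remains is that the article commits to comparing sites, every method it names for that is unadjusted, and it says the design makes the cross-country comparison effective. Separate breakdowns by site and by age leave the overall contrast unadjusted, and crossing the two is not stated.

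A reader might infer that age differences between sites will show up as differences in disease burden. The article does not support that, because it gives no age structure by site. The range of 5 to 7 households per village suggests that household size varies, but household size does not give the share of older people. Nor should high rejection rates be taken as typical: they need an age gradient steeper than the one assumed with Table 1's 20% and a wide gap in age structure.

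**Conclusion.** The point holds as a conditional one. The tests named for the between-country contrast are unadjusted and no adjustment is tied to it, so overall differences in age-dependent outcomes may partly reflect age and sex structure. The Discussion's claim of effective cross-country comparison needs more than representative sampling.

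The size cannot be fixed from the article. With Table 1's 20% at 50 or over and an assumed 10% at 15–49, the artefact is small: 0.5 to 2 points, with rejection in about 5% to 20% of surveys. With an assumed 40% it reaches 1.5 to 6 points and 11% to 82%. It vanishes if the sites share an age structure or the outcome does not depend on age, and it matters less for indicators confined to a narrow age band, such as anaemia under 5 years. Single-site prevalence estimates are not affected.

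**What to change.** Keep crude weighted prevalence as the burden estimate for each site. For between-country contrasts of outcomes that span wide age ranges, add to "Planned analysis" that one of the following will also be reported:

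- directly age- and sex-standardised prevalences on one common standard (for example, the pooled household-roster population), with design-based confidence intervals; or
- marginal predictions from a survey-design model containing site, age and sex.

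In the Discussion, rest the cross-country claim on these estimates and describe the crude figures as local burden.

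The cost is a little more analysis and slightly less precise contrasts. No new data are needed, since age and sex are already collected, and the household head supplies them for non-responders.

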**Figure 1 F1:**
[figure not shown]
The study sites and population of the cross-sectional household health survey conducted by the South and Southeast Asia Community-based Trials Network (SEACTN). The Bangladesh site includes 130 villages from Cox’s Bazar and Bandarban districts; the Cambodia site includes 82 villages from Battambang and Pailin provinces; and the Thailand site includes 179 villages located in Chiang Rai province. HHS, The Household Health Survey.

A two-stage cluster sampling will be used to obtain a representative sample from each study site. In the first stage, 75 villages will be selected using the probability-proportional-to-size sample method.^15–17^ For the second stage, within each village, a simple random sample of 5–7 households (adjusted to the average household size) will be selected using computer-generated random sampling from the village household list.

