#### Inclusion and exclusion criteria

For each selected household, all usual household members or visitors who stayed overnight in the households before the survey are eligible to be enrolled.^18^

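### The sample size allows for village clustering, but the planned analysis names tests that assume independent people and carries forward only sampling weights

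*Protocol article*

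**What the plan says.** All of this is in the Protocol article.

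- **Design (Study population and setting).** The sample is clustered: "A two-stage cluster sampling will be used to obtain a representative sample from each study site". Villages are the units drawn at stage one: "In the first stage, 75 villages will be selected using the probability-proportional-to-size sample method". Households are drawn next, from the list kept for each sampled village: "a simple random sample of 5–7 households (adjusted to the average household size) will be selected".
- **Enrolment (Inclusion and exclusion criteria).** Whole households are taken: "For each selected household, all usual household members or visitors who stayed overnight in the households before the survey are eligible to be enrolled".
- **Sample size (note to Table 1).** "Design effect of 1.5 is used to account for a slightly expected increase in variance due to clustering".
- **Planned analysis.** Outcomes are reported by country with 95% confidence intervals, and compared across sites and participants' "characteristics using appropriate tests, such as the Student’s t-test, Mann-Whitney U tests or χ^2^ tests". Univariate and multivariate models are to explore associations. The section's one reference to the survey design is "Sampling weights will be accounted for, as needed, in the analysis".

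The article does not say that any test, interval or model allows for village or household clustering, and it does not say how the intervals are computed.

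**The concern.** People in one village, and more so in one household, tend to share exposures, infections, diet and wealth. The sample size section accepts that this raises the variance. The analysis section then gives three examples of tests, and all three ignore it in their standard form.

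The sentence on weights does not fill the gap. Weights correct for unequal chances of selection and leave the correlation between neighbours and relatives untouched. A probability-proportional-to-size draw with a roughly constant number of households per village is also close to self-weighting within a site. An analyst could reasonably decide that weights are not needed there, and then nothing of the cluster design would reach the analysis.

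The contrasts most exposed are ones the article relies on. The Discussion says that the design supports cross-country comparison, and it looks to household wealth for insight into health disparities. Neither site nor household wealth varies within a household.

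**Working it through.** **Inputs from the article.** 75 villages; 5–7 households per village; 4.5 persons per household; 1500 expected participants per country (1667 after allowing for 10% non-response); design effect (DEFF) 1.5; 95% confidence level for reporting, so z = 1.96.

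**1. The plan's own figure.** n = DEFF × z² × p(1 − p)/d². For the overall row of Table 1 (p = 0.20, d = 0.05): 1.5 × 3.8416 × 0.16/0.0025 = 368.8, against the stated 369. The design effect is therefore really used in the sample size.

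**2. Is 75 the number per site?** 75 × 5 × 4.5 = 1,688, close to 1667 per country. As a total over three sites, even 75 × 7 × 4.5 = 2,363 would fall far short of 3 × 1667 = 5,001. So 75 is per site, with 1500/75 = 20 participants per village.

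**3. Intraclass correlation implied by the plan.** (DEFF − 1)/(m − 1) = 0.5/19 = 0.026 at m = 20.

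**4. True size of an unadjusted between-site chi-square test.** If the true variance is DEFF times the assumed one, the statistic is inflated by DEFF, so size = P(χ² > critical value/DEFF).
- Two sites, 1 df: 3.8415/1.5 = 2.561, giving 0.1095, or about 11.0%.
- Three sites, 2 df: 5.9915/1.5 = 3.994, giving 0.1357, or about 13.6%.

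A simulation with 75 villages of 20 people per site, prevalence 20% and intraclass correlation 0.026 gave 11.2% and 13.4%.

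**5. Coverage of a simple-random-sample 95% interval.** 1.96/√1.5 = 1.600, so coverage is 1 − 0.1095 = 0.89 (simulation 89.0%). A design-based interval is √1.5 = 1.22 times as wide. At p = 20% and n = 1500 the half-width is 2.5 percentage points instead of 2.0.

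**6. Type of factor compared (simulated, nominal 5%).**

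| Factor | Assumed clustering | True size |
|---|---|---|
| Balanced within villages (e.g. sex) | village only, 0.026 | 4.8% |
| Household-level | village 0.026 plus household 0.1 | about 11% |
| Village-level | village 0.026 plus household 0.1 | about 15% |

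The household value of 0.1 is an assumption. For a factor such as sex, shared village and household effects fall on both groups and largely cancel in the difference. An unadjusted test is then about right or conservative.

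**7. Age subgroups.** Fewer people per village means less inflation. With the correlation of 0.026, village clustering only, and the expected numbers in Table 1:

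| Age group (years) | Per village | DEFF = 1 + (m − 1) × 0.026 | Two-site size |
|---|---|---|---|
| <5 | 150/75 = 2 | 1.03 | 5.3% |
| ≥50 | 300/75 = 4 | 1.08 | 5.9% |
| 15–49 | 750/75 = 10 | 1.24 | 7.8% |
| ≥15 | 1050/75 = 14 | 1.34 | 9.1% |

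Household clustering would add to these.

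**8. Sensitivity to the design effect (assumed range).** From 1.1 to 3, two-site size runs from 6.2% to 25.8%, and simple-random-sample coverage from 93.8% to 74.2%.

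**The case against.** The list of tests is introduced as examples of appropriate ones, so a design-adjusted chi-square is not excluded. The primary objectives are prevalences, and the named tests concern comparisons. Variance estimation for a survey is commonly left to the full protocol or the analysis plan, neither of which is shown. Many sociodemographic factors, sex above all, vary within households, where the error is small. Several outcomes (blood pressure, HbA1c, cholesterol, hepatitis C) are measured only from age 15, where fewer people share a village.

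Much of this stands, and it limits the point. A reader might infer that all the p-values and all the 95% confidence intervals will be wrong. The documents do not support that. No interval method is given, so the loss of coverage is conditional on a simple-random-sample formula. The inflation of p-values is clear only for contrasts between sites, villages and households. Nor do the results at design effects of 2 or 3 describe this plan, which expects only a slight increase in variance.

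What does not stand is that the matter is merely left open. The article goes into method: it gives three tests, none of which respects the design in standard form, and one design feature, weights, which does not deal with clustering. Someone following the text as written gets an analysis at odds with the sample size section.

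**Conclusion.** The point holds in this form: the analysis text does not carry forward the clustering that the sample size allows for. If the tests are run as named, comparisons across sites and across village- or household-level characteristics are anti-conservative, with a true size of about 11% (two sites) or 13.6% (three sites) at a nominal 5%. These figures rest on the plan's design effect of 1.5 applying to the outcome compared and on the full sample of 1500 per site. They are smaller in age subgroups if only village clustering operates. The 89% coverage is what would follow from simple-random-sample intervals; it is not a forecast of what the sponsor will do.

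**What to change.** In Planned analysis, replace the named tests and the sentence on weights with a statement that all prevalences, confidence intervals, comparisons and regression models use design-based estimation, with site as stratum, village as primary sampling unit, and sampling weights. Name the methods:

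- proportions: Rao-Scott adjusted chi-square;
- means: Wald tests from survey-weighted regression;
- medians: a design-based rank test;
- univariate and multivariate models: fitted under the same design.

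Variance computed between villages also takes in correlation within households, since households are nested in villages.

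In Cambodia 75 of 82 villages are drawn, so intervals without a finite-population correction would tend to be too wide. If a correction is used, it must suit the probability-proportional-to-size draw, in which villages do not all have the same chance of selection, and it must keep the household-stage variance. A plain factor of 1 − 75/82 = 0.085 on the whole variance does neither and would make intervals too narrow.

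The cost is analysis wording, standard survey software and somewhat wider intervals (1.22 times those of a simple random sample at the planned design effect). Sampling and fieldwork do not change.
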